## **7. STUDY MEDICATION**

### **7.1 Dosing of azithromycin**

Azithromycin (Zithromax) will be made available as labelled study drug (label: azithromycin/placebo 500 mg) by the Sponsor and will be stored at room temperature (not above 30 °C). Dosage form: white, capsule-shaped, film-coated 500 mg tablet, packed in one blister for 3 tablets.

Placebo (film-coated maltodextrin): will be made available by the local pharmacy and labelled as azithromycin/placebo 500 mg packed in one blister for 3 tablets.

## **7.2 Instructions for the use of azithromycin(placebo**

One weekly dose of azithromycin 1500 mg orally will be applied (3 x 500 mg pills of azithromycin weekly, taken on a single day), with days 1, 8, 15 and 22 constituting one treatment cycle. Two cycles given every 28 days are planned. It is not required to administer any pre-medication for treatments with azithromycin. Placebo will be applied in a similar way, i.e. 3 tablets daily once a week days 1, 8, 15 and 22 for two cycles every 28 days (total of 8 weeks)

## **7.3 Packaging and labelling**

The sponsor is responsible to provide the shipping orders. Azithromycin/Placebo will be provided and labelled by the sponsor of this trial. The drugs will be provided to the sponsor in individual pharmaceutical packings. Study medication must be dispensed in the original packaging with the label clearly visible. Each pharmaceutical packing will identify the contents as study medication and bear protocol number. In addition, the label will bear the sponsors name, quantity contained, a package number and the standard caution statement as follows: Caution: New drug - Limited by Federal law to investigational use. The study drug label must be clearly visible.

## **7.4 Receipt of the study drug**

The investigator or designee is responsible for taking an inventory of each shipment of study drug received and comparing it with the accompanying study drug accountability form. The investigator will verify the accuracy of the information on the form, sign and date it, retain a copy in the study file. The numbers of pharmaceutical packings must be recorded when drug is received and dispensed.

## **7.5 Storage**

At the study site, all investigational study drugs for oral use will be stored in a locked, safe area to prevent unauthorized access. The study drug should not be stored above 30 °C.

## 7.6 Unused supplies

Returned or unused study drug will be transferred to the hospital pharmacy and destroyed due to local SOP's. If any study drug is lost or damaged, its disposition should be documented in the source documents and Drug Dispensing LOG.

## 8. STUDY PROCEDURES

### 8.1 Screening and eligibility

The Investigator is responsible for keeping a record of all subjects who sign an informed consent form (ICF) for entry into the study. All subjects will be screened for eligibility. Investigations at baseline and during the study are outlined below. Study Assessments, unless otherwise specified, must take place within 28 days prior to initiation of therapy. Screening pregnancy tests for women of childbearing potential must occur within 7 days before first application of investigational medical product (IMP). Before screening, a negative SARS-COV-2 PCR not older than 28 days must be present.

### 8.2 Study treatment

Patients will be randomized in 1:1 ratio in Arm A or B:

Arm A: continued oncological therapy plus azithromycin (Zithromax) 1500 mg orally once a week for 8 weeks in the absence of documented SARS-COV2 infection or adverse events

Arm B: continued oncological therapy plus placebo 3 tablets orally daily once a week for 8 weeks in the absence of documented SARS-COV2 infection or adverse events

### 8.3 Study procedures

#### At baseline (within 28 days prior to first treatment)

- Written informed consent
- Complete medical history including oncological medical record
- Assessment of the oncological treatment plan
- Documentation of concomitant medication

- Physical examination and ECOG status assessment
- ECG including assessment of QTc
- Hematology (complete blood count, differential)
- Routine serum biochemistry including procalcitonin and IL6
- Pregnancy test in women of childbearing-potential
- Nasal swab for resistance testing at baseline

Investigations during the study (study visits on day one of each antineoplastic treatment cycle or on day 28 latest) and at end of treatment

- Assessment of adverse events and concomitant medication
- Hematology (complete blood count, differential)
- Routine serum biochemistry including procalcitonin and IL6
- Pregnancy test in women of childbearing-potential
- ECG with assessment of QTc
- Nasal swab for testing of azithromycin-resistant bacterial strains at Visit 1 and 2 (latest week 4 and 8)

PCR for SARS-COV-2 from nasal swabs taken every 28 days is part of the routine care of patients; however, results will be used for defining infection with SARS-COV-2.

#### **8.5 Treatment compliance and drug accountability**

At all times, study drug will be prepared and administered by study site personnel, and patients will be given study for one treatment cycle (i.e. 4 weekly doses) every 28 days. Patients are asked to bring any left-over medication back to the study site. Quantity and LOT-numbers of used vials/pharmaceutical packings must be recorded on “Drug Dispensing LOG´s” and in the source documents.

## **8.6 Concomitant therapy**

Subjects should receive full standard of care, including transfusions of blood and blood products and antiemetics when appropriate. No specific concomitant medication is prohibited, but all compounds have to be documented appropriately.

## **9. PREMATURE WITHDRAWAL**

### **9.1 Premature trial termination**

Any patients who experience a serious adverse event may be withdrawn at any time from the study at the discretion of the investigator. If any serious disadvantage of the treatment becomes evident during the clinical trial, therapy will be terminated. In this case the necessary procedures will be arranged to ensure protection of the subjects' interests.

### **9.2 Replacement policy**

A total of N=200 patients, i.e. 100 per treatment group, will be enrolled into the study; If patients are withdrawn for reasons other than SARS-COV2 infection within the first 4 weeks of the study (i.e. before the first response evaluation), they will be replaced.

## **10. STATISTICAL CONSIDERATIONS**

### **10.1 Sample size calculations**

Reliable sample size planning is challenging because of the unpredictability and dynamics of the incidence rates in this epidemic. However, upper bounds for the accuracy of confidence bounds and lower bounds for the power of hypothesis tests can be given. For the sample size calculation, asymptotic z-tests and chi-squared tests were used (the actual analysis will account for time trends in the incidence rates).

For this **phase 2 study** the sample size is chosen based on feasibility arguments. With a **total sample size of 200** the two-sided confidence interval for the difference in proportions will at most extend 0.14 from the point estimate (computed with the large sample normal distribution). If the null hypothesis of equality of proportions is tested with a 2-sided chi-squared test at level 0.05, the power is at least 81% if the true treatment effect is 20 percentage points (e.g., incidence rates of 30% in the treatment and 50% in the control group). If the difference is 15 percentage points the power is at least 56%.

Distance of two-sided 95%-confidence bound to the observed value for the difference in proportions (large sample approximation)

| Sample Size (total)                     | 100  | 200   | 400  | 600   | 800   |
|-----------------------------------------|------|--------------|------|-------|-------|
| Distance of CI from observed proportion | ±0.2 | ±0.14 | ±0.1 | ±0.08 | ±0.07 |

Power to for the chi-squared test the test the null hypothesis of equal proportions (2-sided significance level 0.05). The power below is calculated assuming the infection rate are symmetrical around 50%, e.g., assuming an effect size of 10 % points would translate to infection rates of 45% and 55%, respectively.

| Effect Size
(Percentage Points) | Sample Size (total) |            |     |     |     |
|--------------------------------------------|----------------------------|------------|-----|-----|-----|
|                                            | 100                        | 200 | 300 | 400 | 800 |
| 7                                          | 10%                        | 17% | 23% | 29% | 51% |
| 10                                         | 17%                        | 29% | 41% | 52% | 80% |
| 15                                         | 32%                        | 56% | 74% | 85% | 99% |
| 20                                         | 52%                        | 81% | 93% | 98% | 99% |

**Recruitment period:** Recruitment period 4 Weeks (50 patients per week), follow-up 12 weeks  
After 200 follow-up tests have been performed (around week 8), an interim and safety analysis will be performed. If very low infection rates, i.e. less than one infection, are observed the trial may be stopped for futility. If the results are promising, the trial might be extended (further details see in section on statistical analysis).

## 10.2 Statistical Analysis Plan

## Analysis Sets

Two different analysis sets are defined

### Modified Intention to treat set (mITTs)

This analysis set includes subjects who were randomized. According to the intent to treat principle, subjects will be analyzed according to the treatment they have been assigned to during the randomization procedure. The mITT includes all patients who are eligible for the study and receive at least one dose of study drug will be included in the analysis. Any patients who enroll into the study but who receive no study medication will be excluded, but a primary analysis will be conducted which will include all enrolled patients (intent to treat population)

### Per-protocol set (PPs)

This analysis set comprises all subjects who received study drug (at least one dose) and did not violate the protocol in a way that might affect the evaluation of the effect of the study drug(s) on the primary objective, i.e., without major protocol violations.

## Baseline parameters and concomitant medications

Baseline parameters, medical history and concomitant medication will be documented during screening and throughout the trial until week X. Enrolment, protocol deviations and discontinuations from the study drug and the study will be summarized. Demographics (age, race, ethnicity and sex) and medical history and study drug administration will also be summarized by treatment group. For qualitative variables (e.g. sex), absolute ( $n =$ ) and relative frequencies will be calculated per treatment group. Data will be visualized by bar plots. For quantitative data (e.g. age), the number of valid observations ( $n =$ ), mean, standard deviation, standard error, median, minimum and maximum will be calculated for each treatment group and each time point separately. Data will be visualized by boxplots and histograms.

## Primary Endpoint Analysis

All primary analyses will be on the ITT set and the analysis based on the per protocol set will be provided as supportive analysis. The primary endpoint is the between group difference in the incidence rate per 4 weeks. We will compute 2-sided 95% confidence bounds for the incidence rates. Furthermore, we test the null hypothesis that the incidence rates in the two groups are equal. To estimate and compare the incidence rates, the test status at weeks 4,8,12 will be modeled using time to event analysis models and will adjusted for calendar time to account for time trends in the incidence rate. The time-to-infection is defined as time from randomization to infection. If patients drop out, their observations will be censored at the last observation time.

This data will be visualized by Kaplan-Meier Plots. For each group unadjusted two-sided 95% confidence intervals will be reported as well.

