#### Primary endpoints:

- Cumulative number of SARS-COV-2 infections as verified by PCR from routine nasal swabs performed every 28 days (symptomatic or asymptomatic) at week 12 after initiation of therapy

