##### 5.2 Inclusion criteria

To be included each patient must fulfill all of the following criteria:

- Histologically confirmed cancer diagnosis
- Active disease in need of antineoplastic therapy
  - o treatment may include classical cytostatic agents, molecular targeted therapy, monoclonal antibodies bevacizumab, cetuximab, rituximab and obinutuzumab (either alone or in combination with chemotherapy) and checkpoint inhibitors
  - o treatment may be ongoing or newly started
  - o oral, intravenous or subcutaneous application route is allowed

- adjuvant, neoadjuvant or palliative chemotherapy is allowed
- the planned treatment duration must be at least 3 months, i.e. 12 weeks
- Age  $\geq 18$  years
- Life expectancy of at least 3 months
- Adequate renal, cardiac and liver function to tolerate the treatment
- Normal QTc ( $\leq 450$  ms) on ECG
- ECOG performance status of  $< 3$
- Negative PCR for SARS-COV-2 not older than 28 days
- Capable of understanding the study and giving informed consent

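### The Kaplan-Meier display in 10.2 makes no provision for death before infection, so read as cumulative infection it runs slightly too high; an Aalen-Johansen curve would match the endpoint

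*Protocol*

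**What the plan says.** The synopsis and protocol section 3.1 define the primary endpoint as a cumulative count at week 12: "Cumulative number of SARS-COV-2 infections as verified by PCR from routine nasal swabs performed every 28 days".

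Section 10.2, Primary Endpoint Analysis, states the target as the difference between arms in a four-weekly incidence rate. The estimate and test come from time-to-event models of the test status at weeks 4, 8 and 12, adjusted for calendar time. Three further sentences matter here:

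- Event time: "The time-to-infection is defined as time from randomization to infection".
- Patients who leave: "If patients drop out, their observations will be censored at the last observation time".
- Display: "This data will be visualized by Kaplan-Meier Plots".

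Unadjusted 95% intervals per group follow directly after the last of these. Death before infection is named nowhere in this part of the plan, and no competing event is mentioned anywhere in the protocol.

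Section 5.2 admits patients on adjuvant, neoadjuvant or palliative chemotherapy and sets the floor "Life expectancy of at least 3 months". All-cause mortality is a secondary endpoint, and overall survival is named among the time-to-event endpoints. No expected death rate is given.

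**The concern.** A Kaplan-Meier curve for infection has two outcomes, event or censored. A patient who dies uninfected is therefore normally censored, and the estimator treats that patient as someone who could still have been infected later. One minus Kaplan-Meier then answers what proportion would be infected if nobody died. The endpoint in section 3.1 asks how many patients are infected by week 12, and a death without infection permanently removes a patient from that count.

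Kaplan-Meier is the only cumulative display that 10.2 names, so a reader will take its week-12 height as the cumulative proportion infected. Section 10.2 also says that the phase II data will set the sample size of any second stage. Proportions read off that curve could be carried into that calculation.

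**Working it through.** **The plan's own figures.** With 100 per arm:

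- Largest half-width of the confidence interval: 1.96 × √(2 × 0.25/100) = 0.139. The plan says 0.14.
- Power for 40% v 60%: Φ[(0.20 − 1.96 × 0.0707)/0.0693] = Φ(0.886) = 81%. The plan says "the power is at least 81% if the true treatment effect is 20 percentage points".
- Power for 42.5% v 57.5%: 56.5%. The plan says at least 56%.

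These reproduce, and nothing below touches them.

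**Inputs for the check.**

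- p is the week-12 infection probability that Kaplan-Meier estimates when deaths are censored. I use 30% and 50%, the plan's example in 10.1, and 5% and 10% as assumed low-incidence cases.
- m is the 12-week probability of death. The protocol gives no value, so 5%, 10% and 20% are assumptions.
- Constant, independent hazards of infection and death over 12 weeks are also assumed.

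**Formula.** With λi = −ln(1−p)/12 and λd = −ln(1−m)/12 per week:

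- 1 − KM at week 12 = p
- Cumulative incidence (CIF) = λi/(λi+λd) × [1 − exp(−12(λi+λd))] = λi/(λi+λd) × [1 − (1−p)(1−m)]

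Example, p = 10% and m = 10%: the hazards are equal, so CIF = 0.5 × (1 − 0.81) = 0.095, against 1 − KM = 0.100.

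Example, p = 30% and m = 10%: 0.3567/(0.3567 + 0.1054) × (1 − 0.63) = 0.772 × 0.37 = 0.2856, against 0.300.

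**CIF, with the relative excess of 1 − KM in brackets.**

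| 1 − KM | m = 5% | m = 10% | m = 20% |
|---|---|---|---|
| 5% | 4.88% (2.6%) | 4.75% (5.3%) | 4.49% (11.5%) |
| 10% | 9.75% (2.5%) | 9.50% (5.3%) | 8.98% (11.4%) |
| 30% | 29.3% (2.4%) | 28.6% (5.0%) | 27.1% (10.8%) |
| 50% | 48.9% (2.3%) | 47.7% (4.7%) | 45.4% (10.2%) |

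At 2% deaths the excess is about 1% relative. At 10% deaths it is 0.25 and 0.5 points at 5% and 10% incidence, and 1.4 and 2.3 points at 30% and 50%.

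**Effect between arms.** With 10% deaths in both arms, a Kaplan-Meier difference of 50% − 30% = 20.0 points corresponds to 47.7% − 28.6% = 19.2 points in cumulative incidence. The cause-specific hazard ratio is ln(0.70)/ln(0.50) = 0.515 at any death rate.

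**Dating by swab.** Over three 4-week intervals, the risk per interval is 1 − 0.70^(1/3) = 0.112 and 1 − 0.50^(1/3) = 0.206. The corresponding continuous hazards per 4 weeks are −ln(0.70)/3 = 0.119 and −ln(0.50)/3 = 0.231. Each pair holds two measures of the same process, and either is a fair reading of a four-weekly rate. In a simulation of 2,000,000 patients with swabs at weeks 4, 8 and 12 and 10% deaths, Kaplan-Meier on the swab weeks returned 0.1005, 0.300 and 0.500 for inputs 0.10, 0.30 and 0.50. The swab grid itself does not distort the curve.

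**The case against.** The strongest reply is that Kaplan-Meier is only a picture. The primary quantity in 10.2 is a rate from a time-to-event model. For a cause-specific rate a patient who dies simply leaves the risk set, so censoring at death is standard. This stands. A reader might infer that the primary analysis is a Kaplan-Meier analysis, or that the primary rate, hazard ratio or test is biased. The protocol supports neither.

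Second, the protocol never says that deaths count as drop-outs, and it leaves further methodology to a SAP that is not shown. This also stands as far as it goes. The remaining point does not depend on that silence, because the protocol itself chooses the Kaplan-Meier display, and this estimator has no separate place for a competing event.

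Third, one might infer that infections are not dated by swab and that the rates are therefore 6% and 11% too low at 30% and 50%. The model uses test status at the swab weeks, which reads naturally as grouped-time data. Those percentages only contrast an interval risk with a continuous hazard. They would be errors only if a continuous-time rate were computed with infections dated at the positive swab, and the protocol does not specify that. What is left is loose wording: neither the infection date nor the last observation is tied to a swab.

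Fourth, the life-expectancy criterion is a floor, combined with ECOG below 3 and at least 12 weeks of planned treatment. It limits early deaths. It does not show that patients expected to die within the window are recruited, only that some deaths are plausible.

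Finally, the size is small. Half a point is half a patient in an arm of 100, against a confidence interval for the difference of up to ±14 points, or about ±7 at 5% v 10% (1.96 × √[(0.0475 + 0.09)/100] = 0.073). The 30% and 50% rates are an example in a lower-bound power statement, not a forecast.

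**Conclusion.** The point holds as a minor mismatch between display and endpoint. The synopsis and section 3.1 ask for cumulative infections at week 12, while the curve chosen in 10.2 overstates the cumulative proportion infected whenever patients die uninfected. The relative excess is about 2.5%, 5% and 10–11% at assumed 12-week mortality of 5%, 10% and 20%, under constant independent hazards. At low incidence with 10% deaths it is at most about half a point.

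It does not reach the primary model, its cause-specific rate, the hazard ratio, the test, or the sample size figures. The dating of infection and censoring needs clarifying but is not shown to be an error.

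**What to change.** In section 10.2, Primary Endpoint Analysis:

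1. Replace the Kaplan-Meier display by Aalen-Johansen cumulative incidence curves of infection, with death before infection as a competing event. Report the week-12 value per arm with its 95% confidence interval. Keep the calendar-time-adjusted, cause-specific time-to-event model for the test.
2. As a clarification only, state that the model is fitted on the swab grid, with infection lying between the last negative and first positive swab (for example a grouped-time complementary log-log model), and that the last observation time of a drop-out means the last negative swab.

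The cost is a few sentences in the protocol or SAP and standard software. PCR results and deaths are already trial outcomes, so no new procedure is needed. The displayed incidence will be slightly lower, and one extra curve, death without infection, will be shown.

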### Secondary Endpoints

- Number of severe COVID-19 cases defined as combined endpoint of hospitalization rate or death at 12 weeks after initiation of therapy
- Severity of COVID-19 cases (see grading by WHO)
- All-cause mortality
- Safety and tolerability of IMP (clinical and laboratory, CTCAE criteria)
- Infections other than COVID-19 including bacterial and viral infections
- Occurrence of azithromycin-resistant bacterial strains

For **binary secondary endpoints** (such all-cause mortality or number of severe COVID-19 cases) absolute ( $n =$  ) and frequencies in percent (%) will be calculated per treatment group. 95%-confidence intervals will be calculated for rates, if appropriate. Such data will be visualized with bar charts. If appropriate, logistic regression models will be applied using treatment as independent factor. Furthermore, the model will be adjusted for sex and age.

For **ordinally scaled endpoints** (such as Grading of COVID-19 cases on day 0, 28 (=week 4), 56 (=week 8) and 84 (=week 12) after randomization) absolute ( $n =$  ) and frequencies in percent (%) will be calculated for all categories separately for each treatment group (and timepoints. If appropriate, treatment groups will be compared with each other by Mann-Whitney-U Tests.

For **time-to-event endpoints** (such as overall survival (OS)) Kaplan-Meier plots will be provided. The two-group will be compared with log-rank Tests. Additionally, similar analysis as for the primary endpoint will be performed.

The analyses of all secondary endpoints are considered as exploratory. Unadjusted p-values and 95%-confidence intervals might be presented for secondary endpoints, but these are for descriptive purposes only and not subject to adjustment for multiplicity.

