## 2.2 COVID-19 in cancer patients

Patients with an active diagnosis of cancer are prone to infections for multiple reasons, ranging from a potentially compromised immune system due the disease itself, tumor cachexia and malnutrition, to immunosuppression as the main side effect of most cancer treatments such as chemotherapy, molecular targeted agents and immunotherapy. A first analysis of a nation-wide cohort of 1590 COVID-19 patients in China identified 18 patients with a history of malignancy and sufficient medical data for detailed analysis , and reported an extrapolated three-fold higher rate of cancer patients within this collective if compared to the normal population (1% versus 0.29%). Furthermore, this analysis documented a significantly higher risk to develop severe symptoms, defined as the percentage of patients admitted to the intensive care unit requiring invasive ventilation or death, if compared to the overall population (39% vs 8%,  $p=0.0003$ ). At particular high risk were patients with active treatment, with three of four patients undergoing antitumor therapy categorized as severe cases. Finally, the authors also reported a more rapid course of the disease with the median time to serious events being 13 versus 43 days ( $p<0.0001$ ). While the numbers in this cohort are limited, these data clearly suggest cancer patients and particularly patients with ongoing treatment as a high risk group for severe COVID-19 manifestations. Whereas additional large cohorts on cancer patients are still lacking, this series identified age, lymphopenia and leucopenia but also concurrent treatment with prednisone as strong predictors of ARDS development and severe clinical course, with all of these factors being relevant in cancer patients . In response to this, Onkopedia , a consensus platform for oncological care in German-speaking countries, has already prompted a specific guideline for managing cancer patients during the COVID-19 pandemic and suggested specific decision criteria for triaging application of anticancer treatments in view of infection risk and underlying cancer disease status.

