### 6.2 Definition of secondary endpoints

Number of patients experiencing severe COVID-19 infection defined as a combined endpoint of hospitalization or death at week 12 after initiation of therapy.

COVID-19 cases are defined as outlined by the WHO, including a PCR for COVID-19 from any specimen (respiratory, blood, urine, stool, other bodily fluids).

Severity of COVID-19 cases: The severity of cases will be classified as suggested in the Blue Print for COVID-19 therapeutic trials by the WHO (range 0-8)

**Table.** Ordinal Scale for Clinical Improvement of COVID-19 (WHO Blueprint).

| Patient state                 | Descriptor                                                  | Score |
|-------------------------------|-------------------------------------------------------------|-------|
| Uninfected                    | No clinical or virologically evidence of infection          | 0     |
| Ambulatory                    | No limitations of activity                                  | 1     |
|                               | Limitation of activities                                    | 2     |
| Hospitalized – mild disease   | Hospitalized, no oxygen therapy                             | 3     |
|                               | Oxygen by mask or nasal prongs                              | 4     |
| Hospitalized – severe disease | Non-invasive ventilation or high flow oxygen                | 5     |
|                               | Intubation and mechanical ventilation                       | 6     |
|                               | Ventilation + additional organ support – pressors, RRT, ECM | 7     |
| Dead                          | Death                                                       | 8     |

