## 11.2 Serious adverse events

A serious adverse event (SAE) is any AE which:

- Results in death
- Is life-threatening (i.e., in the opinion of the Investigator(s) the subject is at immediate risk of death from the AE)
- Requires inpatient hospitalization or prolongation of existing hospitalization
- Results in persistent or significant disability/incapacity (a substantial disruption of the subject's ability to conduct normal life functions)
- Is a congenital anomaly/birth defect
- Constitutes an important medical event

Important medical events are defined as those occurrences that may not be immediately life threatening or result in death, hospitalization, or disability, but may jeopardize the subject or require medical or surgical intervention to prevent one of the other outcomes listed above. Medical and scientific judgment should be exercised in deciding whether such an AE should be considered serious. Events not considered to be SAEs are hospitalizations which: were planned before entry into the clinical study; are for elective treatment of a condition unrelated to the studied indication or its treatment; occur on an emergency outpatient basis and do not result in admission (unless fulfilling other criteria above); are part of the normal treatment or monitoring of the studied indication and are not associated with any deterioration in condition. If an AE is considered serious, both the AE pages of the CRF and the SAE Report Form must be completed. For each SAE, the Investigator will provide information on severity, start and stop dates, relationship to study drug, action taken regarding study drug, and outcome.

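### COVID-19 severity is graded at days 0, 28, 56 and 84 with no worst-score rule, so a non-fatal peak that resolves between grading days is recorded at a lower grade

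*Protocol*

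**What the plan says.** Protocol section 6.2 makes severity of COVID-19 cases a secondary endpoint: "The severity of cases will be classified as suggested in the Blue Print for COVID-19 therapeutic trials by the WHO (range 0-8"). It prints the scale, from 0 for an uninfected patient through ambulatory (1-2) and hospitalised (3-7) to death (8). It says neither when the score is taken nor which score counts if several are available.

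The only timing is in section 10.2, Secondary Endpoints, in the paragraph on ordinal endpoints: "Grading of COVID-19 cases on day 0, 28 (=week 4), 56 (=week 8) and 84 (=week 12) after randomization". Category frequencies are given per arm and time point, and "If appropriate, treatment groups will be compared with each other by Mann-Whitney-U Tests".

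Three other statements bear on the point:

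- Section 6.2 has a separate secondary endpoint: "Number of patients experiencing severe COVID-19 infection defined as a combined endpoint of hospitalization or death at week 12 after initiation of therapy".
- Section 11.2 counts as serious any adverse event that "Requires inpatient hospitalization or prolongation of existing hospitalization", and asks for start and stop dates.
- Section 10.2 adds: "The analyses of all secondary endpoints are considered as exploratory".

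**The concern.** The WHO scale records the state a patient is in on the day of assessment. Every score except death can fall again as the patient recovers, down to 0. The grading days are counted from randomisation and have no relation to the date of infection. With 28 days between gradings, a patient can deteriorate and recover without being seen at the worst grade.

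As an illustration, a patient infected on day 32, on high-flow oxygen on day 42 (score 5) and home by day 54 is graded somewhere between 0 and 2 on day 56. In the day-56 table that patient looks like one who was never more than mildly ill.

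At stake is the information that a nine-level scale adds to a yes/no endpoint, namely how ill the non-fatal cases became. Reducing severe illness is one of the trial's stated aims (synopsis, scientific rationale), so the measure should be able to show it.

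**Working it through.** **Plan's own figure.** The protocol gives no figure for the severity endpoint. Its confidence-interval and power tables in section 10.1 concern infection proportions and do not bear on this point.

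**Inputs**

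- Grading days 0, 28, 56 and 84 after randomisation (section 10.2), so the gap is 28 days.
- Scheduled visits give no finer grid that can be relied on. Section 8.3 sets "study visits on day one of each antineoplastic treatment cycle or on day 28 latest", so they may be up to 28 days apart.
- Death is score 8 and persists, so it is seen at the next grading day (section 6.2 scale).
- Speed of illness: section 2.2 on COVID-19 in cancer patients reports "the median time to serious events being 13 versus 43 days", the shorter time being for cancer patients. This is a time to an event. It shows that deterioration can fall inside one 28-day interval, but not how long a severe state lasts.
- Duration L of the non-fatal state: not given in the documents. Assumed range 3 to 28 days.

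**Step 1: chance that a non-fatal state is missed.** If the state starts at a uniformly random time relative to the grid, it covers a grading day with probability min(1, L/28). The chance of a miss is

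P(miss) = max(0, 1 - L/28).

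| Assumed L (days) | Covers a grading day | Missed |
|---|---|---|
| 3 | 3/28 = 11% | 89% |
| 5 | 5/28 = 18% | 82% |
| 7 | 7/28 = 25% | 75% |
| 10 | 10/28 = 36% | 64% |
| 14 | 14/28 = 50% | 50% |
| 21 | 21/28 = 75% | 25% |
| 28 | 100% | 0% |

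A simulation with start times uniform over days 0 to 84 and gradings at 28, 56 and 84 gave capture of 10.7%, 17.9%, 25.0%, 35.6%, 49.9%, 75.0% and 100%, which agrees with the formula.

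If L is read as the whole hospital stay, the missed share is a lower bound for missing the peak. A stay can include a grading day while its worst phase does not.

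**Step 2: allow for deaths.** If a fraction f of severe cases die, and deaths are always captured, the share of severe cases missed is (1 - f)(1 - L/28). Both values of f are assumptions.

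| L (days) | f = 20% | f = 40% |
|---|---|---|
| 7 | 0.8 x 0.75 = 60% | 0.6 x 0.75 = 45% |
| 10 | 0.8 x 0.64 = 51% | 0.6 x 0.64 = 39% |
| 14 | 0.8 x 0.50 = 40% | 0.6 x 0.50 = 30% |
| 21 | 0.8 x 0.25 = 20% | 0.6 x 0.25 = 15% |

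**Step 3: what the other endpoints recover.** I read hospitalisation or death at week 12 as counted cumulatively per patient, since section 6.2 counts patients who experience it. The patient in the illustration is then a severe case on that endpoint. It is binary, however, and does not separate score 3 (in hospital without oxygen) from score 7 (ventilation with further organ support), or score 1 from score 2. That gradation is what the snapshots can lose and no other endpoint supplies.

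**Step 4: worst score instead.** A maximum taken over randomisation to day 84 captures every documented peak by construction, whatever L is.

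**The case against.** The strongest reply is that the protocol does not confine grading to these days. They stand in a parenthesis that offers COVID-19 grading as an example of an ordinal endpoint, section 6.2 names no days, and section 10.2 leaves further methodological detail to a SAP that is not at hand. A worst-score summary could be there. Part of this stands: sections 6.2 and 10.2 are not reconciled on timing. But the example is the choice of endpoint. The four days themselves are listed in full, and they are the only timing that the protocol gives. Followed as written, it produces snapshots.

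A second reply is that the scale is titled as one of clinical improvement, so tabulating current state at scheduled times is a recognisable use. That is fair for description. It does not answer how severe the cases were when the times are unrelated to infection.

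A third reply is that the important contrast is covered elsewhere, by hospitalisation or death, all-cause mortality and SAE reporting, and that every secondary analysis is exploratory. This stands and limits the consequence.

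Several stronger readings are tempting, and the documents do not support them:

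- That the endpoint misses most severe illness. This holds only for non-fatal states shorter than 14 days, and the protocol gives no duration.
- That the 13-day median proves short episodes. It is a time to an event, not a duration.
- That the day-0 grade is empty because entry needs a negative PCR. That test may be up to 28 days old, so a patient may be infected on day 0.
- That the treatment contrast is largely removed. Some dilution is plausible, but no effect or power on the ordinal scale has been calculated.

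**Conclusion.** The point holds in a limited form. Section 10.2 grades a current-state scale every 28 days from randomisation, and neither 6.2 nor 10.2 has a worst-score rule, so non-fatal peaks that resolve between gradings are recorded at a lower grade. The missed share is 1 - L/28: 75%, 50% and 25% at assumed durations of 7, 14 and 21 days, and smaller as a share of all severe cases once deaths are counted. The calculation rests on start times unrelated to the grading days and on durations that the protocol does not give.

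The loss falls mainly on the gradation among non-fatal cases (ambulatory 1-2, hospitalised 3-7). The endpoint is secondary and exploratory, and the primary conclusion is unaffected. The change is worth making because it is cheap and the present measure can fail at its own purpose.

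**What to change.** In sections 6.2 and 10.2:

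- Define severity as the worst WHO score of each randomised patient from randomisation to day 84, taken from hospital and adverse event records, with uninfected patients at 0 as on the protocol's own scale.
- Compare the arms once on this score.
- State that the comparison combines infection and severity. With uninfected patients at 0, the target is no longer severity among cases alone, and a difference could come from fewer infections, milder infections or both.
- Tabulate the worst score among infected patients by arm, descriptively.
- Keep the grades at days 0, 28, 56 and 84 as description only.

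The cost is wording in two sections, one case report form field (worst score with its date) and chart review of infected patients. The trial has a single centre, and admissions are in general already reported as SAEs with dates. Sample size, visits and treatment do not change.
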